### Evaluation of Exercise Capacity in ICU Survivors

The ICU-CARE CPET protocol provides critical insights into both systemic cardiorespiratory dynamics that can influence exercise capacity [5,7,21-24,41] and local microvascular insights provided by NIRS technology [49,50] to quantitatively assess cardiopulmonary and skeletal muscle oxygenation responses during exercise. Data will be reported as mean (SD) or mean (95% CI) for the cohort, as well as disaggregated according to biological sex. The quality of the fitting will be assured by the analysis of residuals, the degree of linear correlation between the experimental data, fitted function (*r*), and the significance level (*P* value) of the estimated parameters. We expect that the standardized, single-session ICU-CARE CPET protocol proposed in this study will enable (1) quantitative evaluation of $\dot{V}O_{2peak}$, $\dot{V}O_{2}$ on/off kinetics, and skeletal muscle microvascular oxygenation in ICU survivors; (2) delineation of physiological relationships between the above variables to characterize the mechanisms of ICU-AW, including physiological heterogeneity between patients; (3) prospective longitudinal assessment of rehabilitation trajectory of individual ICU survivors after critical illness; and (4) comparison with other populations (eg, healthy, older adults, and chronic diseases).

### Statistical Analysis and Sample Size Calculation

In order to calculate a sample size for this study based on statistical testing, we have selected the Bland-Altman agreement [65] between predicted and measured $\dot{V}O_{2peak}$ as the target variable of interest. This was chosen because it is the first outcome variable that is being calculated based on a priori equations and the ICU correction factor (see Equation 1). We estimate sample size using the method described by Lu et al [66], whereby a sample size of 48 participants is needed to detect a standardized agreement limit (*δ*/*σ*) of 2.9 and a standardized difference limit (*μ*/*σ*) of 0.2, with *α*=0.05 and *β*=0.2 (80% power). With this method, *δ* is the maximum acceptable agreement limit, *μ* is the mean difference, and *σ* is the standard deviation of differences between predicted and measured $\dot{V}O_{2peak}$. Because this is the first application of these physiological equations, the true *σ* of the population will only be ascertained after study completion, and will inform sample size calculation for future studies. Further testing of secondary statistical outcomes, including sex-disaggregated and sensitivity analysis, is not directly informed by sample size and should be considered hypothesis generating. As a result, these subgroups will likely be underpowered until evaluation in larger studies.

For longitudinal testing of the same participant at different timepoints (ie, 6 and 12 months), changes in quantitative exercise, kinetic, and NIRS variables will be reported as absolute and %change between sessions; statistical differences between sessions will be calculated with the Wilcoxon signed-rank test, with a significance level set at *P*<.05. Because only a subgroup of participants will be completing both sessions, the results from this longitudinal analysis will be used to inform the design of future studies.

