### Recruitment Strategy

Before ICU discharge, researchers will screen potential participants for willingness to join follow-up, meeting the inclusion criteria. After 3 months post-ICU discharge, participants will be contacted through telecommunication to determine their ongoing willingness and ability to participate in the ICU-CARE CPET study, with transportation compensation provided within the city limits. Participants will receive detailed information regarding procedures and potential risks before agreeing to attend (please refer to the Pre-CPET Evaluation section below). Due to the high degree of functional impairment and inherently dynamic transitions in care after ICU discharge, we intend for initial participation in the ICU-CARE CPET study to occur at 6 months after ICU discharge, with a range of ±1 month. Participants’ electronic medical records and telephone conversations will be screened for relevant hospital and postdischarge information regarding length of ICU stay, readmission(s), intubation period, concurrent illness, list of medications, and to acquire a recent blood test if available. Participants will then be asked, “How many floors can you walk up quickly without stopping?,” to prescribe the Watt/min increment for the ramp portion of the test (please see Incremental Phase below for more details). Participants will be given an option to be tested again at 12 months after ICU discharge to track their recovery, but this is not required for the main purpose of the study design.

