With exercise starting at zero, subsequent analysis will be performed using a mono-exponential model to fit the pulmonary or primary component of the $\dot{V}O_{2}$ response (ie, phase II) by skipping the cardiogenic phase (ie, phase I), as previously recommended [33,58], left-shifting at 20 s in length [52]. Then, the steady-state $\dot{V}O_{2}$ (SS $\dot{V}O_{2}$ or phase III) will be calculated as the average of the last 2 minutes of the CWR exercise phase [28]. The mono-exponential fitting is characterized by $\dot{V}O_{2}$ parameters, including tau (τ), time delay (TD), amplitude A_0_ and A_1_, and mean response time (MRT), where τ is defined as the time constant of the exponential function, representing the time taken to reach 63% of the steady-state or final value; TD records the delay to the exponential response start (ie, phase II) (the model is not constrained to pass through the origin) before oxygen uptake responds to exercise; A_0_ represents the baseline value (resting $\dot{V}O_{2}$), whereas A_1_ represents the change of amplitude from baseline to steady-state $\dot{V}O_{2}$ (ie, SS $\dot{V}O_{2}$ – baseline value); and MRT, defined as TD + τ, representing the overall time to adjust the rate of $\dot{V}O_{2}$ to changes in workload [28]. At the end of the incremental phase, $\dot{V}O_{2peak}$ will be defined as the highest value of the last 30 seconds before volitional exhaustion after applying a 20-second moving average [59,60]. The quality of the fitting will follow our previous protocol [28]. The analysis of residuals, the degree of linear correlation between the experimental data and fitted function (*r*), the 95% CI band, and the significance level (*P* value) of the estimated parameters are used to determine the quality of the fitting.

The HHb signal will be normalized using a 60-second average before the exercise begins, then analyzed by detecting the nadir, occurring after a sudden decrease in HHb signal, to exclude data not associated with muscular $\dot{V}O_{2}$ dynamics, referring to the muscle pump [61]. After the nadir, HHb increases monoexponentially, representing the $\dot{V}O_{2}$ dynamics during the onset of exercise [27,62-64].

The HHb monoexponential function is expressed in the equation below:

$$HHb\;{\left(t\right)}^{\;}=HHb_{bl}+a\left[1-e^{-\left(t-TD\right)/\tau }\right]$$

where HHb_bl_=HHb baseline, *a*=amplitude, *e*=mathematical constant, *t*=time, TD=time delay, and τ=time constant.

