MRT of the HHb is also estimated by the sum of τ and TD, to determine the MRT time constant.

Changes in TSI will be assessed by calculating the difference between baseline (average 30 seconds before CWR) and end of exercise (30-second average before start of recovery) to quantitatively evaluate tissue saturation fluctuation of oxygen uptake within the skeletal muscle, reported as ΔTSI [%] in the equation below:

$$\Delta TSI\;\left[\%\right]={TSI}_{peak}-{TSI}_{bl}$$

where TSI_peak_=30-second average before $\dot{V}O_{2peak}$; TSI_bl_=TSI baseline, 30-second average before commencing exercise.

Secondary variables from the CPET will be collected in an exploratory manner. These include carbon dioxide output ($\dot{V}{CO}_{2})$, respiratory exchange ratio, oxyhemoglobin, heart rate response, peak oxygen pulse, tidal volume, breathing frequency, minute ventilation (VE), ventilatory efficiency (VE/VCO_2_), and breathing reserve. Measured adipose tissue thickness of ≥12.5 mm will define a subgroup of patients with less reliable skeletal muscle NIRS measurements [37]; sensitivity analysis will be undertaken with both inclusion and exclusion of this subgroup in cohort outcomes. Other variables to consider include the CPET time of completion, patient-reported outcomes, and any other additional comments regarding the ICU-CARE CPET protocol experience.

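### Reporting %change for every longitudinal variable gives a sign-reversed or unstable figure for ΔTSI, possibly an unstable one for TD, and can bias the summary for noisy kinetic variables (minor)

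*Protocol article*

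**What the plan says.** The 12-month visit is optional; the Recruitment Strategy section says that "this is not required for the main purpose of the study design". For those who attend both visits, Statistical Analysis and Sample Size Calculation sets one reporting rule: "changes in quantitative exercise, kinetic, and NIRS variables will be reported as absolute and %change between sessions". It adds that "statistical differences between sessions will be calculated with the Wilcoxon signed-rank test", without naming the scale on which the test is run, and that "the results from this longitudinal analysis will be used to inform the design of future studies".

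The variables under this rule differ in kind. Under Data Analysis:

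- **ΔTSI** is a within-session difference: "Changes in TSI will be assessed by calculating the difference between baseline (average 30 seconds before CWR) and end of exercise". The formula is TSI at peak minus TSI at baseline, in percentage points.
- **TD** is a fitted parameter of a mono-exponential model in which "the model is not constrained to pass through the origin". No lower bound is given.
- **τ** is the fitted time constant, and **MRT** is TD plus τ.
- **HHb amplitude** is a fitted change from a normalised baseline.

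The longitudinal paragraph names no summary statistic for %change. Evaluation of Exercise Capacity in ICU Survivors says, of the cohort data, "Data will be reported as mean (SD) or mean (95% CI) for the cohort".

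**The concern.** Percentage change makes sense for a quantity with a true zero that stays clear of zero. ΔTSI does not meet that condition: it is negative when saturation falls during exercise, can be close to zero, and can be positive. Dividing by it reverses the sign for participants with a negative 6-month value, keeps it for those with a positive one, and inflates the figure for those near zero. TD could behave in the same way if some fitted delays fall near or below zero.

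For τ and similar positive quantities the sign is safe. The 6-month value is both the comparator and the divisor, however, so measurement error in it pushes an average of individual %changes upward even when nothing has changed.

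The stated use of these results is to inform later studies. Their planners will take effect sizes and directions from the table. A %change column that contradicts the absolute column, or that suggests slower kinetics because of noise, would serve them badly.

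**Working it through.** The protocol gives no figure on this point. Its one calculation (48 participants, for Bland-Altman agreement) does not bear on it. It also states no within-person SD or CV and no expected number of returning participants, so every size below rests on assumed inputs.

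**1. Sign of %change for ΔTSI.** Let x be the 6-month value, y the 12-month value and d = y − x. Then %change = 100·d/x, which has the opposite sign to d whenever x < 0. Three illustrative participants with the same absolute change of −5 points:

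| 6 months | 12 months | Absolute change | %change |
|---|---|---|---|
| −5 | −10 | −5 | 100·(−5)/(−5) = +100% |
| −0.5 | −5.5 | −5 | 100·(−5)/(−0.5) = +1000% |
| +1 | −4 | −5 | 100·(−5)/(+1) = −500% |

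**2. How often this occurs for ΔTSI, with no true change** (normal model).

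- *Mean −8, between-person SD 5, within-person SD 3.* The SD of one session's value is √(25 + 9) = 5.83. P(x < 0) = Φ(8/5.83) = Φ(1.37) ≈ 0.915, and simulation gave 92% of individual %changes with the opposite sign to the absolute change. About 19% exceeded 100% in size. With 20 pairs, the 5th to 95th percentile range of the mean %change was −196% to +189%.
- *Mean −15, between-person SD 5, within-person SD 2.* The SD is √(25 + 4) = 5.39 and Φ(15/5.39) = Φ(2.79) ≈ 0.997, so the sign is almost always reversed, but consistently. Only 1.4% exceeded 100% in size. Apart from its sign, %change is usable here.

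**3. TD, with no true change** (assumed mean 10 s, between- and within-person SD 5 s each). The SD is √(25 + 25) = 7.07 and P(x < 0) = Φ(−1.41) ≈ 0.08. In simulation 25% of individual %changes exceeded 100% in size, 8% had the opposite sign to the absolute change, and the average %change did not settle (−15% in one run, +143% in another).

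**4. Positive noisy variables such as τ, with no true change.** Take y = m·e₂ and x = m·e₁ with independent log-normal errors of log-scale variance s². Then E[y/x] = exp(s²/2)·exp(s²/2) = exp(s²) = 1 + CV², so the expected %change is 100·CV².

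| Within-person CV | 100·CV² | Simulated mean %change |
|---|---|---|
| 10% | 1.0 | about +1.0 |
| 20% | 4.0 | about +4.0 |
| 30% | 9.0 | about +9.0 |
| 40% | 16.0 | about +16.0 |

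The median %change stayed between 0.0% and 2.2% in the same simulations, and the geometric mean ratio showed about 0%. For VO2peak (assumed mean 20, within-person SD 1) the bias was about 0.3%.

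**5. The planned test.** With no true change, the Wilcoxon test on paired absolute differences rejected 4 to 6% of the time in every scenario. For ΔTSI and TD the same held on the %change scale. For τ-like variables, a test run on %change instead rejected 5 to 6% with 12 pairs, 6 to 8% with 24 and 6 to 11% with 48. A 95% CI for the mean %change excluded zero in 5 to 6%, 6 to 13% and 7 to 32% of data sets respectively, the upper ends being at a CV of 40%.

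**The case against.** A reader might infer that the plan will declare change between 6 and 12 months where there is none. The documents do not support that. The only between-session inference is a Wilcoxon signed-rank test, which keeps its error rate near 5% on paired values. False findings would need a step that the protocol does not state: a confidence interval on the mean %change, or the test run on %change. Even then the excess is small at 12 to 24 pairs unless within-person CV is 30% or more, and 48 pairs would mean that every participant returned.

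A reader might also infer that %change is meaningless for all NIRS and kinetic variables. That is too strong. If ΔTSI is consistently well below zero, its %change is stable, and a move from −5 to −10 shown as +100% can be read as desaturation having doubled. Nothing in the protocol shows that fitted TD values will be near zero or negative.

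Three further points stand. Absolute change is already planned for the same variables. The mean of individual %changes is an inference, because the sentence naming means is in another section. And the 12-month visit is optional.

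What survives is narrower. The protocol states a rule without exceptions, so this is not detail left to an analysis plan. For ΔTSI the rule produces a column whose sign contradicts the column beside it. Having the absolute change alongside limits the harm but does not resolve the contradiction.

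**Conclusion.** The point holds in a limited form and is minor. For ΔTSI the sign reversal is arithmetic and applies to every participant with a negative 6-month value. How unstable the figure is depends on how close 6-month values come to zero: 19% of individuals beyond ±100% under one assumed set of values, 1.4% under another. TD may share the instability. For τ-like variables the upward bias is about the squared within-person CV, and only if individual %changes are averaged. VO2peak is practically unaffected.

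The consequence is a descriptive effect size that could mislead planners of later studies. It is not a false test result, and it does not touch the feasibility outcome or the sample size. Because the documents give neither within-person variability nor the number of returning participants, the actual size cannot be fixed from them.

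**What to change.** In Statistical Analysis and Sample Size Calculation, replace the single rule with three statements:

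1. For ΔTSI, TD and any other variable that can be zero or negative, report absolute change only.
2. For variables that are positive in all participants, such as VO2peak and τ, report absolute change plus the geometric mean of the 12-month to 6-month ratio with its 95% CI, or the median %change. MRT and HHb amplitude belong here only if all fitted values are positive, since MRT includes TD and the amplitude is a fitted change.
3. Run the Wilcoxon signed-rank test on paired absolute values.

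The cost is a short edit to the text, with no new data, visits or participants. The downside is that readers lose the %change figure for ΔTSI and TD.

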### Dissemination Policy

Research staff will communicate the results of exercise testing to participants at the time of their test. The researcher will then offer a digital copy of the CPET printed from the metabolic cart sent via email, excluding confidential information (eg, name). Results of the study are anticipated to be published when the study is completed.

## Discussion

### Rationale for Protocol Development

This study introduces the ICU-CARE CPET: a standardized protocol combining $\dot{V}O_{2peak}$, $\dot{V}O_{2}$ on/off kinetics, and skeletal muscle microvascular oxygenation measurements in ICU survivors. Designed to overcome limitations of traditional exercise methodology [28] (eg, multiple hospital/research lab visits, longer data collection, recruitment, and compliance issues), and recognizing that this field is evolving [7,28], we propose to combine CPET with $\dot{V}O_{2}$ kinetics, improving overall research efficiency within clinical settings [7], empowering further investigation of ICU-AW and its associated pathophysiology.

Expanding beyond a focus on skeletal muscle biology, ICU-AW is now believed to be multifactorial [1,22,67,68]. As demonstrated with other diseases such as congestive heart failure, we propose that the syndrome of ICU-AW (ie, impaired locomotive capacity) likely represents a failure of integrated systems that coordinate oxygen delivery, terminal microvascular-myocyte oxygen exchange, and skeletal muscle mitochondrial oxygen utilization [69]. This point of view has led to a shift of research from local skeletal muscle biology toward global investigation of the integrative physiologic responses across the oxygen delivery pathway [6]. Consequently, we are proposing the incorporation of CPET and NIRS to quantitatively assess cardiopulmonary and skeletal muscle microvascular oxygenation responses during exercise.

Currently, there is a lack of standardization for combining assessments of $\dot{V}O_{2peak}$, $\dot{V}O_{2}$ on/off kinetics, and skeletal muscle NIRS post-ICU discharge. This protocol was developed based on the study of Longobardi et al [7] and our own work with healthy control populations [28], both exploring single-session CPET for the combined assessment of $\dot{V}O_{2peak}$ and on/off kinetics. Longobardi et al [7] used a single-session treadmill CPET incorporating a 3-minute moderate-intensity walk (below ventilatory anaerobic threshold) before the incremental phase and a 6-minute recovery period in survivors of severe COVID-19 3‐6 months after hospitalization (n=53). The limitations of their study were the uniform application of the CWR power for all participants, the relatively short period of time for on/off kinetics, which may not achieve steady state, and the absence of NIRS measurements to evaluate skeletal muscle oxygenation. We expanded on this protocol with a standardized and single-session cycle ergometer protocol and tested it in healthy young adults (n=20). This CPET protocol consisted of 3 minutes of rest seated in a chair ($\dot{V}O_{2}rest)$, 3 minutes of baseline seated on the cycle ergometer (no pedaling), 5 minutes of CWR at 30% estimated $\dot{V}O_{2reserve}$ (60 rpm), incremental phase (20 W min^−1^) to attain $\dot{V}O_{2peak}$, and 10 minutes of passive recovery. Based on the results, it was concluded that the proposed protocol was feasible and appropriate for the evaluation of the intended variables. Although not included in our healthy control study, NIRS data were also collected and are being analyzed separately to ensure data quality and reliability.

Research suggests that 1 of 3 ICU survivors experience reduced $\dot{V}O_{2peak}$ [21], often falling below 80%‐85% of predicted values [5,21,22] during the first year after ICU discharge. Based on these studies, we have decided to use a correction factor of 0.75 (75%) to account for the reduced $\dot{V}O_{2peak}$ in the ICU survivor population. This is incorporated into Equation 1 (in step 1) and will be evaluated during this study. We have also adapted the incremental phase of this protocol (W) based on patients’ self-reported functional status (5, 10, 15, or 20 W min^−1^), derived from a practical guide for CPET [56], suggesting the use of the staircase question to inform ramp modifications. Research suggests a linear relationship shared between the number of steps climbed, minute ventilation, and $\dot{V}O_{2peak}$ [68]. Our practical staircase question [56] will be compared with the mMRC using a correlational analysis within the prospective study, offering a tailored approach to promote inclusion. In future studies, analysis of the statistical significance correlation between mMRC and staircase question steps can be conducted to assess its relationship, depending on sample size, to get a significant result, to validate the staircase question to be used instead of the mMRC scale, or in conjunction.

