### Incremental Phase

The incremental phase of the protocol will be based on the information obtained from the self-reported staircase question [56] and modified Medical Research Council (mMRC) dyspnea scale [57] during the recruitment process. For the staircase question, participants will be asked, “How many floors can you walk up quickly without stopping?,” during the recruitment process. Based on their responses, the increments will be defined as follows: one floor (5 W min^−1^; 50 W), two floors (10 W min^−1^; 100 W), three floors (15 W min^−1^; 125‐150 W), and four floors (20 W min^−1^; 200 W). For the mMRC dyspnea scale, participants’ severity of breathlessness will be reported based on activity descriptors and mMRC grade between 0 and 4 with their respective Watt equivalent, as described in Table 1. Participants will cycle until the termination criteria are met, as described above.

**Table 1. T1:** Modified Medical Research Council (mMRC) dyspnea scale.

Grade	Activity descriptor	Ramp
0	Strenuous activity, not troubled by breathlessness (eg, cycling and shoveling heavy snow)	20 W min^−1^
1	Walking up an incline causes shortness of breath	15 W min^−1^
2	Walking two blocks and experiencing breathlessness	10 W min^−1^
3	Walking short distances and needs to catch breath (eg, 100 ft, or room to room)	10 W min^−1^ for males, 5 W min^−1^ for females
4	Cannot get dressed or shower without shortness of breath	No CPET^a^

a CPET: cardiopulmonary exercise test.

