### Validation of ICU-Specific Protocol Adaptations

We will determine whether our ICU correction factor of 0.75 is an acceptable method for estimating $\overset{˙}{V}O_{2peak}$ from population equations. The statistical analysis for comparisons between predicted versus measured variables—specifically $\dot{V}O_{2peak}$ and $\dot{V}O_{2CWR}$—will be performed with (1) percentage differences between predicted and measured variables for general weighted inspection of the difference, (2) linear regression/correlational analysis with measured variables as the dependent and predicted as the independent variable, (3) Bland-Altman analysis [65] to assess the agreement between predicted and measured variables, and (4) Cohen *d* test to assess the size of the difference/similarity between predicted and measured variables; the difference between measured and predicted values will be considered clinically significant (ie, discordant) if they exceed a Cohen *d* value of 0.5. The statistical significance level will be set at *P*<.05.

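### The staircase question and the mMRC scale are compared by correlation only, which cannot show that they prescribe the same ramp, yet a significant correlation is named as a possible future route to substitution

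*Protocol article*

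**What the plan says.** Two statements stand next to each other in the Discussion of the protocol article (Rationale for Protocol Development).

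- **This study.** The staircase question "will be compared with the mMRC using a correlational analysis within the prospective study". No coefficient, threshold or decision rule is attached.
- **Later work.** "In future studies, analysis of the statistical significance correlation between mMRC and staircase question steps can be conducted to assess its relationship". Subject to sample size, the aim given is "to get a significant result, to validate the staircase question to be used instead of the mMRC scale, or in conjunction".

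The Incremental Phase section and Table 1 convert both instruments to a ramp rate. The staircase answer gives 5, 10, 15 or 20 W/min for one to four floors. Breathlessness is recorded as an "mMRC grade between 0 and 4 with their respective Watt equivalent, as described in Table 1": grade 0 gives 20, grade 1 gives 15 and grade 2 gives 10 W/min. Grade 3 gives "10 W min^−1^ for males, 5 W min^−1^ for females", and grade 4 means no exercise test. No analysis of agreement between the two prescribed ramps is described.

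**The concern.** The question that the Discussion raises is whether one instrument can stand in for the other. Both exist in this protocol to choose a ramp, so substitution is justified only if they choose the same ramp, or nearly so, for the same person. A correlation test has no association as its null hypothesis. Two self-reports of exertional limitation are likely to be associated whether or not they lead to the same ramp, and a systematic shift between them leaves the correlation untouched.

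The ramp based on self-reported functional status is one of the four elements of the standardization listed in the Conclusions. If later work adopted the staircase question because of a significant correlation, participants could be put on systematically different ramps without the analysis showing it. The present study would have collected the data to detect this but would not have looked.

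**Working it through.** **1. Is there a figure in the plan to reproduce?** None is given for this comparison. The only calculated sample size, 48, is for Bland-Altman agreement of predicted and measured peak oxygen uptake (δ/σ = 2.9, μ/σ = 0.2, α = 0.05, power 80%). A non-central t calculation gives 46, with 82.5% power at 48, so that figure is close to reproduced. It was not derived for the staircase comparison.

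**2. Perfect correlation with no agreement.** This uses only the maps in the Incremental Phase section and Table 1.

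| Floors | Ramp from floors (W/min) | mMRC grade | Ramp from mMRC (W/min) | Difference (W/min) |
|---|---|---|---|---|
| 1 | 5 | 2 | 10 | −5 |
| 2 | 10 | 1 | 15 | −5 |
| 3 | 15 | 0 | 20 | −5 |

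The rank correlation is −1 (more floors is better, a higher grade is worse). Exact ramp agreement is 0%. No distributional assumption is needed, and grade 3, the only sex-specific row, is not involved.

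**3. Disagreement built into the maps.** For men, grades 0 to 3 give 20, 15, 10 and 10 W/min, and grade 4 gives no test. The value 5 W/min does not occur. Every man who answers one floor is therefore discordant whatever his grade. As an illustration, assume 60% men, each of the four answers given by 25% on each instrument, and perfect rank concordance. Then 0.60 × 0.25 = 15% of participants still differ. A correlation of the raw scores cannot show this.

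**4. What a significant correlation would require.** The critical value is r = t / √(n − 2 + t²), two-sided 5%.

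- n = 48: t = 2.013, so r = 2.013 / √(46 + 4.052) = 0.285, or r² of about 8%.
- n = 100: r = 0.197.
- n = 200: r = 0.139.

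The threshold falls as n grows. A larger later study would thus find it easier to declare validation with no better agreement. The n = 48 figure is for scale only, since the plan sets no significance test for this comparison in the present study.

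**5. How often might ramps differ?** The documents give no category frequencies and no expected correlation, so these are assumptions: latent bivariate-normal scores, n = 48, 60% men, Table 1 applied with its sex-specific row. The last column gives the share of participants on different ramps as the latent correlation rises from 0.3 to 0.9.

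| Assumed use of categories | Share on different ramps |
|---|---|
| Four equally used | 69% falling to 44% |
| Middle-weighted | 62% falling to 36% |
| Staircase shifted to low ramps, mMRC to mild grades | 76% to 80% throughout |
| 60% of participants in one category | 50% falling to 27% |

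With equal categories and latent correlation 0.5, the Spearman test was significant in 90% of simulated studies while 64% of participants had different ramps. The overall range is about 27% to 80%.

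**6. Precision of an agreement estimate at N = 48.** The half-width is 1.96 × √(p(1 − p)/48).

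- p = 0.80: 1.96 × 0.0577 = 0.113, or ±11 points.
- p = 0.50: 1.96 × 0.0722 = 0.141, or ±14 points.

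**The case against.** The strongest reply is that nothing in this study turns on the comparison. It is not a listed primary or secondary outcome, it carries no decision rule, and the sample size section describes further secondary testing as hypothesis generating. A correlation is a legitimate first description of two related scales. The significance test is optional, is placed in future studies, and joint use is offered as an alternative to replacement. All of this stands, and it keeps the severity low.

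Two stronger readings are tempting, and the documents support neither.

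- **That this study will declare the instruments interchangeable on P<.05.** The statement "The statistical significance level will be set at *P*<.05" belongs to the comparisons of predicted with measured values. The Discussion attaches no such rule to the staircase comparison here.
- **That most participants would be sent to a different ramp.** This depends on category frequencies that the documents do not give. With most people in one category, discordance was 50% or less. The high figures under shifted categories come largely from the assumed shift itself. For example, take four ramp categories used 40/30/20/10% by one instrument and 10/30/35/25% by the other. Even perfect rank concordance then gives an exact match of only 10 + 0 + 5 + 10 = 25%.

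Nor do the documents say that a different ramp would change measured peak oxygen uptake, and the point does not need it.

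What the reply does not remove is that the only criterion named for substitution is one that cannot establish it. The team already uses the better approach elsewhere: for predicted and measured peak and constant-work-rate oxygen uptake, the validation section plans Bland-Altman agreement in addition to correlation.

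**Conclusion.** The point holds in a limited form. The comparison planned in this study is a correlation only, and the route named for possible later validation is a significant correlation. Neither can answer whether the staircase question may replace the mMRC scale. The counterexample of perfect correlation with 0% agreement, and the certain mismatch for men answering one floor, follow from the article's own maps without assumptions. The size of the problem in practice is unknown: the range of about 27% to 80% discordance rests on assumed category frequencies, sex mix and latent correlations. No stated outcome, sample size or conclusion of this study is affected. It is an inexpensive improvement of low severity.

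**What to change.** 1. Keep the correlation as a description and add an agreement analysis on the ramp. Convert each answer to W/min by the Incremental Phase section and Table 1, including the sex-specific row, and cross-tabulate. Report exact agreement and the share differing by two or more steps, each with a 95% CI, a weighted kappa, and the mean signed difference in W/min. Show any grade 4 response as its own row, since it maps to no ramp.
2. In the sentence on future studies, replace the significant correlation with an agreement criterion, set in advance, for using one instrument instead of the other.
3. State that the maps conflict for men answering one floor. The Recruitment Strategy section ties the ramp to the staircase answer, whereas the Incremental Phase section bases it on both instruments. The investigators should reconcile these passages; no ramp is proposed here.

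The cost is a sentence or two. The sample size does not change, and both answers are already to be obtained during recruitment. The drawback is precision: the interval of about ±11 to 14 percentage points at N=48 should be stated with the result.
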